### Cervical length assessment

Clinical staff will perform transvaginal ultrasound assessment of CL using a GE Voluson E10 ultrasound machine and 7.5MHz transvaginal probe. All measurements will be performed with the woman in a supine position with an empty bladder in the sagittal plane measuring from the internal to external cervical OS. The full length of the cervical canal will be visualized with the closed portion of cervix remaining being measured in triplicate.

The shortest CL measurement of the three readings will be documented as the final CL measurement for that study visit. CL measurements will be known to both the participant and clinician at the time of assessment and will be used to guide ongoing surveillance and PTB intervention as per the clinical team decision-making and regional guidelines.

The study procedure order is further outlined in the study flow chart (Fig 1) and schedule of study procedures (Table 1). Participants will remain in the study for a maximum of 31 weeks, from initial visit to PTBC until point of discharge after delivery, or infant aged 1 month. Assessments will take place at specified timepoints as shown in the study schedule (Table 1).

**Table 1 pone.0316297.t001:** Schedule of Study Procedures.

Order of Procedures	At PTBC triage (12 weeks)	Study Visit A (14+0−17 + 6 weeks)	Study Visit B (18 + 0−21 + 6 weeks)	Study Visit C (22 + 0−25 + 6 weeks)	Postnatal & End of study
*Patient Eligibility*	**X**				
*Patient information Leaflet provided*	**X**				
*Informed Consent*		**X**			
*Pre-Sample Collection Questionnaire*		**X**			
*High Vaginal Swab Collection (2 gifted samples)* * *optional*		**X**			
*Cervical Stiffness Measurement*		**X**	**X**	**X**	
*Cervical Length Scan*		**X**	**X**	**X**	
*Post-Assessment Patient Questionnaire*		**X**			
*Delivery Outcomes*					**X**
*Maternal Postnatal Outcomes*					**X**
*Neonatal Postnatal Outcomes*					**X**
*Adverse Event Reporting*		**X**	**X**	**X**	**X**

### Study outcome

The Pregnolia System is a novel device with no published data providing cervical stiffness index results in asymptomatic women who are high-risk for PTB. This will be the first study to provide this data and will guide how further research using this novel assessment tool can be most appropriately designed.

Previous studies at this study site over the last 10 years have achieved acceptable recruitment when obtaining blood samples and have demonstrated a notable PTB rate in a similar asymptomatic high-risk population (18%) [29,30]. However neither can be extrapolated to the PRECISION study due to the difference in study procedures and change in clinical practice over this time following the introduction of the Saving Babies Lives Care Bundle V3 [3]. Subsequently, this feasibility study will provide an accurate recruitment rate demonstrating this population’s acceptability for this unique assessment in clinical practice. This study will provide an updated outcome incidence of PTB in this appropriately phenotyped study population and an estimate of the variance for cervical stiffness using the Pregnolia System. Together this data will infer the design of a larger study to establish a predictive model for spontaneous preterm birth (<34 weeks) in this patient population [31–33].

### Feasibility outcomes

Our feasibility outcomes of interest relate to whether the study procedure is acceptable, participant adherence and retention to the study is achieved, data collection is feasible, and that cervical stiffness assessment fidelity is maintained with adequate reliability and safety[34].

Our feasibility outcomes will be defined as follows;

1)Participant acceptability of cervical stiffness assessment in PTB clinica.Qualitative questionnaire following assessmentb.Number of participant withdrawals throughout the study duration (aim for < 20%)c.Reasons for non-participation collected of eligible women approached for the study2)Adherence to the protocola.Measured as number of protocol deviations3)Adherence to data collectiona.Numbers of missing data (aim for < 10%).b.Loss to short term follow up (aim for < 5%)4)Safety outcomesa.Incidence of adverse events5)Cervical stiffness fidelitya.Ability to obtain triplicate cervical stiffness measurements (aim for > 90%)b.Triplicate measurement reliability (aim for > 0.8 Cronbach’s Alpha)6)Inputs for sample size and power calculation of future studya.Determine sPTB rate in the total study population (participating and non-participating PTBC patients) to inform current sPTB rate post national guidance care implementationb.Determine estimate of CSI variance using the Pregnolia Systemc.Determine recruitment rate to the study to inform sample size required

### Clinical outcomes

Clinical outcome data will be collected in accordance with the international clinical Delphi consensus on the core outcome data set for PTB in asymptomatic women [35]. The primary clinical outcome is PTB < 34 + 0 weeks gestation. We will define PTB as labour having occurred with either intact membranes or PPROM (<37 + 0 weeks). This excludes iatrogenic causes for preterm delivery including induction of labour (in the absence of PPROM) or elective caesarean section. Secondary maternal and neonatal outcomes will be collected for descriptive analyses only.

### Study endpoint

The study will end when the last recruited woman has delivered and both herself and her baby have been discharged from hospital, or 1 month after delivery, whichever is sooner and all planned analysis of collected data has taken place.

### Statistical analysis

Descriptive statistics will be generated and presented as means (SD), median (IQR) and frequency of observations (percentages) with 95% confidence intervals as appropriate.

Cronbach’s Alpha will be used to assess the reliability of the device to produce consistent readings at different time points. It compares shared variability among the measurements with the overall variance. If the device is reliable then there should be high covariance amongst the measurements relative to the variance. Cronbach’s alpha alongside descriptive statistics with 95% confidence intervals will inform best use of the triplicate CSI measurements taken at each study visit. Specifically exploring whether the first, average, median or lowest measurement of the three readings should be utilised in further analysis and most importantly inform best use of the CSI results in clinical practice.

An estimate of the variability in the outcome measure will be calculated and then applied to a sample size calculation for a further definitive study.

Diagnostic performance of cervical stiffness assessments using the Pregnolia System for PTB will be demonstrated through receiver operating characteristic curves with area under the curve and 95% confidence intervals being calculated, as well as aiming to define the optimum cut-off value for predicting PTB. Cervical length diagnostic performance data will also be generated for direct comparison.

Any association between cervical stiffness and gestational age at delivery will be explored using scatter plots and linear regression. Longitudinal data will be explored using time series plots, and box plots with a sensitivity analysis completed on all participants with a complete data set.

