**Fig 1 pone.0316297.g001:**
[figure not shown]
Study Flow Chart.

Participants will complete a structured questionnaire after their first clinical examination in the study. This questionnaire will collect patient experience of the cervical stiffness assessment in comparison to standard CL assessment and collate data as to the acceptability of the assessment in this patient population (supporting information S1 Fig). Participants attending at Study Visit A time point will be invited to consent to gifting two high vaginal swabs as samples for future vaginal-microbiome research. These gifted samples will be obtained during the speculum procedure used for cervical stiffness assessment.

All study participation will coincide with the participants routine PTBC appointments, and participants will continue to receive all PTB intervention and surveillance as guided by their clinicians and as per national and regional PTB guidance (SBLCBV3, NICE Preterm Labour and Birth guidelines and the North West Regional network PTB guideline) [1,3,26]. Study procedures at each visit are detailed and explained in the study flow chart (Fig 1).

In this feasibility study we will recruit patients for 15 months and expect to achieve a cohort of 60 patients based upon expected high-risk clinic referrals and an assumed recruitment rate of 40%.

Participants will remain in the study following recruitment until delivery and discharge from hospital. Study outcomes will be collected from electronic hospital records for the participant and their baby.

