## Study objective

The PRECISION study has the following objectives

To obtain cervical stiffness measurements during the second trimester in high-risk singleton participants to:Determine the reliability and best interpretation of triplicate measurements in this patient group at this gestation.Explore any potential association between second trimester cervical stiffness and gestation at delivery.Compare cervical stiffness assessments to CL measurements taken concurrently and explore the association with gestation at delivery.•To explore the acceptability of this assessment tool in this patient population for PTBC screening.•Upon positive conclusion of the PRECISION feasibility study, to inform for the design of an appropriately powered study to assess the capability of this novel device for PTB prediction.

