### Cervical stiffness assessment

Cervical stiffness will be measured using the Pregnolia System. Following informed consent, all measurements will be performed with the woman in a supine position with an empty bladder. A vaginal speculum will be placed to visualise the cervix and the single-use, sterile Pregnolia Probe is placed on the anterior lip of the cervix at 12 o’clock position. A recording of cervical stiffness is generated over a maximum of 60 seconds (typically ~15 seconds) and displayed as CSI in mbar. The measurement is repeated 3 consecutive times without any time lag. The clinician is audio-guided by the control unit which indicates when a reading has been taken.

The cervical stiffness readings will be stored on the Pregnolia Control Unit and only documented for the participant once all study procedures have been completed during that study visit. The cervical stiffness readings are blinded to the patient and the clinician at the time of the study visit.

Any difficulty in obtaining readings will be documented on the case report form (CRF). Simple troubleshooting guidelines will be followed to optimize readings at the time of the study visit as per Pregnolia Instructions (e.g., avoiding kinks in connector cable and ensuring Luer locks are secure).

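### The alpha > 0.8 target describes only the mean of three stiffness readings, so alone it cannot support using the first, median or lowest reading

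*Protocol article*

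**What the plan says.** At each visit the device is applied three times: "The measurement is repeated 3 consecutive times without any time lag" (Cervical stiffness assessment). The first listed aim is to "Determine the reliability and best interpretation of triplicate measurements in this patient group at this gestation" (Study objective).

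Feasibility outcomes item 5b gives the fidelity criterion: "Triplicate measurement reliability (aim for > 0.8 Cronbach’s Alpha". The Statistical analysis section describes the same statistic with a different emphasis: "Cronbach’s Alpha will be used to assess the reliability of the device to produce consistent readings at different time points". It then gives alpha a second job: "Cronbach’s alpha alongside descriptive statistics with 95% confidence intervals will inform best use of the triplicate CSI measurements taken at each study visit". The candidates are named: "Specifically exploring whether the first, average, median or lowest measurement of the three readings should be utilised in further analysis". The section adds that the result should guide clinical use of the index.

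The article names no agreement statistic, no within-woman error in mbar and no rule for choosing among the four candidates. Such detail can sit in an analysis plan that is not shown. The statistic, the threshold and the purpose, however, are fixed in the text.

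**The concern.** The target and the decision it feeds concern different quantities. Alpha on a triplicate describes the mean of three. Three of the four candidates are something else: one reading, the middle reading or the smallest. A device could meet the target and the first reading could then be adopted, with the stated reliability wrongly credited to it.

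Alpha is also blind to a uniform shift from the first to the third reading. Because the same tissue is aspirated three times in immediate succession, an order effect is a natural thing to check.

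The chosen summary matters downstream. It enters the ROC curves, the cut-off, the regression on gestation at delivery and the variance estimate for the future sample size (Feasibility outcomes item 6b).

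**Working it through.** **Inputs.** Target alpha = 0.80 (Feasibility outcomes 5b); k = 3 readings per visit (Cervical stiffness assessment); n = 60, from "expect to achieve a cohort of 60 patients" (Study design). The 0.8 is a threshold without derivation, so there is no plan figure to reproduce.

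**1. Single-reading reliability at the target.** For parallel readings, Spearman-Brown gives alpha = k·r / (1 + (k − 1)·r), so r = alpha / (k − (k − 1)·alpha).

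- alpha = 0.80: r = 0.80 / (3 − 1.60) = 0.571
- alpha = 0.90: r = 0.90 / (3 − 1.80) = 0.75
- For r = 0.80: alpha = 2.40 / 2.60 = 0.923

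**2. Consequence for the variance estimate.** Set the total variance of a single reading to 1. At the boundary, 0.571 is between women and 0.429 within. The variance of the mean of three is 0.571 + 0.429/3 = 0.714 (check: 0.571/0.714 = 0.80). A single reading therefore has 1/0.714 = 1.40 times the variance of the mean.

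**3. Uniform shift between readings.** Adding the same constant to every woman's second reading, and another to every third reading, leaves all variances and covariances unchanged, and so leaves alpha unchanged. The absolute-agreement ICC for a single reading is 0.571 / (1 + v), where v is the variance of the three reading means. The shift sizes are illustrative assumptions; the documents give none.

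| Shift per reading (total SD) | v | Alpha | Single-reading absolute agreement |
|---|---|---|---|
| 0 | 0 | 0.80 | 0.57 |
| 0.25 | 0.0625 | 0.80 | 0.54 |
| 0.5 | 0.25 | 0.80 | 0.46 |

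A simulation of 400,000 women gave the same values.

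**4. Can one alpha value rank the four candidates?** With alpha held at 0.80 and no shift, the squared correlation of each summary with the true value was simulated under four assumed error shapes.

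| Error shape | First | Mean | Median | Lowest |
|---|---|---|---|---|
| Normal | 0.57 | 0.80 | 0.75 | 0.70 |
| Exponential (right-skewed) | 0.57 | 0.80 | 0.79 | 0.92 |
| Lognormal | 0.58 | 0.80 | 0.87 | 0.97 |
| t, 3 df | 0.56 | 0.80 | 0.85 | 0.59 |

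The best summary is the mean, the lowest, the lowest and the median in turn, at the same alpha.

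**5. Precision.** The Feldt 95% interval is 1 − (1 − alpha)·F, with F quantiles on 59 and 118 degrees of freedom. At alpha = 0.80 and n = 60 it runs from 0.69 to 0.87. An observed alpha of about 0.87 is needed for the lower limit to reach 0.80. This is context, not a fault of alpha: an ICC from 60 women would be similarly uncertain.

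**The case against.** Much of the case on the other side stands.

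- **Alpha is not used alone.** A reader might infer that the plan lets alpha choose the summary by itself. It does not: alpha is read alongside descriptive statistics with confidence intervals, and the choice is exploratory. Means by reading position would show a large shift. First versus average can also be partly inferred from alpha, by the Spearman-Brown step above.
- **No drift is documented.** A reader might infer that the device drifts. The article says only that readings follow one another without delay. A step of 0.25 SD costs little (0.57 to 0.54).
- **A common shift does limited harm here.** If every woman is measured with the same summary, a constant offset leaves her rank, the AUC and the regression slope unchanged. It moves the cut-off, which is estimated on that same summary. A consistency measure is therefore defensible for those analyses. Absolute agreement matters when reading positions are treated as interchangeable, or when a cut-off set on one summary is applied to another.
- **The sections need not contradict each other.** A reader might take the reference to different time points to mean alpha across visits, where differing true softening would count as unreliability. It can equally mean triplicate consistency at each visit, and the same paragraph speaks of triplicates at each visit.
- **The threshold is an aim.** No stop or go rule is attached to it.

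What these points do not answer is that the numerical target rests on alpha alone, and alpha gives no figure for the median or lowest reading.

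**Conclusion.** The point holds in a limited form. The target measures the consistency of the mean of three readings only. At its boundary a single reading has reliability 0.57, and alpha of about 0.92 would be needed for a single reading to reach 0.80. The target cannot register a shift common to all women, and alpha alone cannot support the first, median or lowest reading.

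The 0.57 assumes parallel readings and is a boundary value, since the aim is strictly above 0.8. The blindness to shift is exact only for a shift shared by all women; one that differs between women would lower alpha somewhat. The shift sizes and error shapes above are illustrations, not findings about this device.

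The documents do not support the stronger conclusions that the device is unreliable or that the ROC and regression analyses would be invalid. Readings are stored, so nothing is lost if the analysis is amended. This is a worthwhile, inexpensive improvement and not a must-fix.

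**What to change.** 1. Within each visit, fit a mixed model with woman as a random effect and reading order as a fixed effect, using all readings obtained. Report the ICC for a single reading and for the mean of three, each as consistency and as absolute agreement, with 95% confidence intervals. Add the within-woman SD in mbar and the mean shift by reading order.
2. Apply the 0.8 target to the reliability of the summary actually carried forward, and say whether it refers to consistency or to absolute agreement.
3. If the median or lowest reading is carried forward, estimate its reliability directly, for example by simulation or bootstrap from the fitted within-woman errors. The single-reading and mean-of-three ICCs do not supply it.
4. In the Statistical analysis section, reword the phrase about time points to mean triplicates within each visit, and report between-visit change separately.

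The cost is analysis wording only, on the same data. The reported reliability may look less favourable than alpha.

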**Discussion:**

This is an exploratory study to assess the use of this novel device in clinical practice. Direct comparison between cervical stiffness assessment using the Pregnolia System and CL assessment will determine the acceptability of this new assessment in this population, as well as explore its potential association with PTB. Our findings from this feasibility study will provide data on the potential of this novel device to impact PTB screening and evaluate acceptability of use in a high-risk population. Data on eligibility, recruitment rates and participant feedback will help inform future study design using the device.

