This feasibility study aims to confirm whether a lower cervical stiffness result obtained using the Pregnolia System has an association with spontaneous PTB in high-risk singleton pregnancies [25]. The study will also directly compare the current gold standard practice of serial CL surveillance in the second trimester to paired cervical stiffness assessments [1]. This study will explore how this device and its’ results can be applied to the population served by the PTB clinic and review acceptability of this assessment in these patients. Together, these results will help inform a future study using the Pregnolia System as a potential predictive tool for PTB.

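### An optimum CSI cut-off chosen and judged on the same 60 or so women, with perhaps 6 to 15 events, will overstate its own sensitivity and specificity and will be unstable; it should be illustrative only

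*Protocol article*

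**What the plan says.** Statistical analysis says diagnostic performance will be shown by ROC curves and AUC with 95% confidence intervals, "as well as aiming to define the optimum cut-off value for predicting PTB". Cervical length (CL) performance is to be produced for direct comparison.

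The same section leaves open whether the first, average, median or lowest of the three CSI readings is used. Cronbach's alpha and descriptive statistics are to inform that choice. CSI is measured at up to three visits, and no visit is named as primary for the ROC. CL is fixed in advance as the shortest of three readings (Cervical length assessment).

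On size, the study design text after Fig 1 says the investigators "expect to achieve a cohort of 60 patients", based on clinic referrals and an assumed 40% recruitment rate. Study outcome gives a PTB rate of 18% from earlier work at the site and then warns: "However neither can be extrapolated to the PRECISION study".

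On purpose, the last paragraph of the Introduction states: "This feasibility study aims to confirm whether a lower cervical stiffness result obtained using the Pregnolia System has an association with spontaneous PTB". The abstract's Discussion states: "This is an exploratory study to assess the use of this novel device in clinical practice". The abstract's Methods, Study objective and Statistical analysis also speak of exploring the association. Study outcome and the main Discussion leave the predictive model to a larger study.

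**The concern.** A cut-off that maximises performance in a sample partly fits the chance features of that sample. When the same women are used to report its sensitivity and specificity, both are too favourable on average, and the bias grows as events become fewer. The cut-off itself can also fall almost anywhere in the middle of the CSI distribution.

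This matters because the article says the data will shape the larger predictive study and that the triplicate work should inform clinical use of CSI results. A threshold published with uncorrected accuracy could be taken into either and would not reproduce. An aim worded as confirmation makes that more likely.

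**Working it through.** **1. The plan's own figure.** The 60 comes from recruitment capacity: 60 / 0.40 = 150 eligible women, or 150 / 15 months = 10 a month. The number of referrals is not given, so 60 cannot be reproduced independently. No effect size, alpha or power is attached to it.

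**2. Events (an assumption).** At 18%: 60 × 0.18 = 10.8, with a binomial 95% range of 5 to 17. The article rejects extrapolating 18% and does not say that it refers to delivery before 34 weeks. The ROC text says only PTB, while Clinical outcomes has a primary outcome before 34+0 weeks and a definition reaching to 37+0. I therefore take a range: 10% gives 6 events and 25% gives 15.

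**3. Precision of the AUC for one CSI measure fixed in advance.** Hanley–McNeil, with m events, n non-events and assumed true AUC A = 0.70:

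SE² = [A(1−A) + (m−1)(q₁−A²) + (n−1)(q₂−A²)] / (mn), where q₁ = A/(2−A) = 0.538 and q₂ = 2A²/(1+A) = 0.576.

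For m = 11, n = 49: (0.21 + 10 × 0.0485 + 48 × 0.0865) / 539 = 0.0090, so SE = 0.095.

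| Events | SE | 95% CI for AUC 0.70 |
|---|---|---|
| 6 | 0.125 | 0.46 to 0.94 |
| 11 | 0.095 | 0.51 to 0.89 |
| 15 | 0.083 | 0.54 to 0.86 |

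The mean AUC over simulated samples was 0.70, so this measure is imprecise but not biased.

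**4. Optimism of the cut-off.** I used the Youden index, J = sensitivity + specificity − 1. In a normal model with AUC 0.70, the group means differ by d = √2 × Φ⁻¹(0.70) = 0.742 SD, and the best achievable J is 2Φ(d/2) − 1 = 0.29. In each simulated sample of 60, one CSI measure at one visit was used, with no selection among summaries or visits. The cut-off with the largest sample J was found, and its true J was then taken from the population.

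| Events | Apparent J | True J at that cut-off | Overstatement | Apparent J of a useless marker (true J 0) |
|---|---|---|---|---|
| 6 | 0.47 | 0.25 | 0.22 | 0.24 |
| 11 | 0.42 | 0.26 | 0.16 | 0.19 |
| 15 | 0.40–0.41 | 0.26 | 0.15 | 0.17 |

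With ten times the data (108 events in 600 women) the overstatement falls to about 0.04 (0.32 against 0.28), so sample size drives it.

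**5. Stability.** With 11 events and AUC 0.70, the chosen cut-off has a 95% range about 2.2 to 2.4 SD of error-free CSI wide across repeat samples. This used a single-reading reliability of 0.57 (which corresponds to alpha 0.8 for three readings, the stated target) or 0.90, and between-visit correlation of 0.3 or 0.6. Even at a fixed cut-off, detecting 8 of 11 events gives an exact 95% CI for sensitivity of 39% to 94%.

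**6. Choice of summary and visit.** If, and only if, the choice were made on AUC (11 events, true AUC 0.70), the best of four summaries at one visit would add about 0.01 to 0.02 to the AUC. The best of 12 (four summaries × three visits) would add about 0.06 to 0.08.

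**The case against.** The strongest reply is that this is a feasibility study sized on recruitment. It words the cut-off as an aim, defers prediction to a larger study and blinds patient and clinician to CSI at the visit. The article condenses a fuller protocol, and internal validation is commonly left to a statistical analysis plan that is not shown. That stands as far as it goes: the absence of an optimism correction from the article is not itself the point. The point is that the article sets out to define an optimum cut-off from a sample that cannot support one.

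A reader might infer that accuracy will be inflated because the best of four summaries at three visits is picked, and that this tilts the comparison with CL towards CSI. The documents do not support that. The choice of summary is tied to Cronbach's alpha and descriptive statistics, not to accuracy, and nothing says a visit will be selected on outcome. The 0.06 to 0.08 gain is therefore a hypothetical worst case. Equally, the text does not rule out an outcome-informed choice: alpha describes the set of three readings and does not rank the four summaries, and the stated blinding covers only the study visit.

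Withdrawals need not reduce the event count much. Withdrawn women are ideally kept for outcome collection, and loss to follow-up is targeted below 5%.

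On the aim, 'confirm whether' can be read loosely as 'find out whether', and no analysis depends on it. It is still out of line with the exploratory wording elsewhere, but it is secondary.

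**Conclusion.** The concern holds for the cut-off. Its sensitivity and specificity, taken together as the Youden index, would be overstated by about 0.15 to 0.22 over 15 to 6 events if the true AUC is 0.70, and a marker with no value would still show about 0.17 to 0.24. The threshold itself would be very unstable. These sizes rest on assumed event rates of 10% to 25%, a normal model, an assumed AUC and a Youden-type optimum. The article names no criterion, and any criterion optimised on the same data has the same kind of problem.

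It does not hold for accuracy in general. The AUC of a CSI measure fixed without reference to outcome is unbiased, though its interval is wide. Added optimism from choosing a summary or visit is a possibility to close off, not something the plan states. About 11 events is an assumption, not a figure the article endorses.

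**What to change.** 1. In Statistical analysis, present any cut-off as illustrative and hypothesis-generating. Give confidence intervals and bootstrap optimism-corrected sensitivity and specificity, repeating the cut-off search in every resample. State that it will not be carried forward as a threshold.
2. State that the CSI summary and the primary visit for the ROC are fixed from measurement properties, blind to delivery outcome, before the ROC analysis and the comparison with CL.
3. In the Introduction, change 'confirm whether' to 'explore whether', in line with the abstract, Study objective and Statistical analysis.

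The cost is a few sentences and a modest amount of extra analysis; no new data are needed. If the analysis plan already contains items 1 and 2, only the article's wording needs to change. The reported accuracy of the cut-off will look less favourable. With so few events the bootstrap corrects the average bias but does not make the cut-off stable, which is why the illustrative label is needed as well.

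### The planned comparison of cervical stiffness with cervical length leans towards stiffness, because only cervical length is disclosed and acted on; it should be labelled as made under length-guided care

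*Protocol article*

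**What the plan says.** Under Statistical analysis, the protocol article plans ROC curves, AUCs with 95% confidence intervals and an optimum cut-off for CSI, followed by: "Cervical length diagnostic performance data will also be generated for direct comparison". A direct comparison of the two assessments also appears in the abstract and the Introduction, and a comparison of concurrent measurements is listed under Study objective.

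The two tests are handled differently during care:

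- CL (Cervical length assessment): "CL measurements will be known to both the participant and clinician at the time of assessment", and the readings "will be used to guide ongoing surveillance and PTB intervention as per the clinical team decision-making and regional guidelines".
- CSI (Cervical stiffness assessment): "The cervical stiffness readings are blinded to the patient and the clinician at the time of the study visit".
- Treatment (Study design): "participants will continue to receive all PTB intervention and surveillance as guided by their clinicians".

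Under Clinical outcomes, the primary clinical outcome is spontaneous preterm birth before 34+0 weeks. It is observed after whatever treatment a CL reading has prompted. The only limitation that the Discussion acknowledges is the single centre.

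**The concern.** This is the treatment paradox in test evaluation. A short CL leads to treatment. If the treatment prevents a birth, that woman has a positive CL test and no event, so she counts against CL. CSI triggers nothing at the visit and is penalised only so far as soft cervices tend also to be short ones. Two tests of equal value would then appear unequal, and the error has a known direction.

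The abstract's Background lists as a weakness of CL that some high-risk women with a short cervix do not deliver preterm. Effective treatment would produce exactly that pattern. The Discussion says the study should help judge how likely the device is to be clinically effective before a powered study is designed and costed. A tilted comparison could therefore colour that judgement, and recruiting more women under the same care would not remove the tilt.

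**Working it through.** **The plan's own figure.** Study design says the team "expect to achieve a cohort of 60 patients based upon expected high-risk clinic referrals and an assumed recruitment rate of 40" per cent. That implies 60 / 0.40 = 150 eligible women over 15 months. The referral count is not given, so 60 can be neither reproduced nor refuted, and nothing below depends on how it was reached. Study outcome gives an 18% preterm birth rate from earlier work at the site and warns that it cannot be extrapolated. At that rate, 60 x 0.18 = 10.8, or about 11 events.

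**Step 1: the mechanism in counts.** Assumptions: per 100 women, the 25 shortest by CL are treated; untreated risk is 21.6%; 49% of untreated events fall in the short group; relative risk (RR) is 0.65.

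| | No treatment effect | RR 0.65 in short-CL women |
|---|---|---|
| Events, short CL | 0.49 x 21.6 = 10.6 | 10.6 x 0.65 = 6.9 |
| All events | 21.6 | 21.6 - 3.7 = 17.9 |
| CL sensitivity | 10.6 / 21.6 = 0.49 | 6.9 / 17.9 = 0.385 |
| CL specificity | 1 - 14.4 / 78.4 = 0.82 | 1 - 18.1 / 82.1 = 0.78 |
| CL positive predictive value | 10.6 / 25 = 0.42 | 6.9 / 25 = 0.28 |

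The test is unchanged. The 3.7 prevented births have moved into its false positives. Simulating this setting with a CSI-CL correlation of 0.3 and equal log-odds of 0.8 per SD gives a CL AUC falling from 0.735 to 0.672 and a CSI AUC falling from 0.736 to 0.717, a gap of +0.045 where the truth is nil.

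**Step 2: a range of assumptions.** Model: CL shortness and CSI softness are standard normal with correlation rho; logit(risk) = c + 0.6 x CL + 0.6 x CSI; c is set so that untreated risk is 18%; risk is multiplied by RR in the shortest 20%. The true gap is zero. Observed gap, CSI minus CL:

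| rho | RR 1.0 | RR 0.7 | RR 0.5 | RR 0.35 |
|---|---|---|---|---|
| 0 | 0.00 | +0.04 | +0.07 | +0.10 |
| 0.4 | 0.00 | +0.03 | +0.05 | +0.07 |
| 0.8 | 0.00 | +0.01 | +0.02 | +0.03 |

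At rho 0.4 the true AUC of each test is about 0.71. With RR 0.5 the observed values are CL 0.63 and CSI 0.68.

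**Step 3: size against noise at 60 women** (rho 0.4, RR 0.5). The mean gap is about 0.05 and the SD of the paired difference about 0.12. CSI has the higher point estimate in about 66% of studies, against 50% with no bias. A two-sided 5% test would reject with probability of about Phi(-1.96 + 0.05/0.12) + Phi(-1.96 - 0.05/0.12) = 0.06 + 0.01 = 0.07. For a single AUC of 0.70 with 11 events and 49 non-events, the Hanley-McNeil standard error is 0.095, so the 95% interval is 0.51 to 0.89.

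**Step 4: do the obvious remedies work?** Same model, rho 0.4:

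- Using only readings taken before treatment: every reading in the model is already pre-treatment, and the gap remains. It is the outcome that has been altered.
- Untreated women only: CL 0.65, CSI 0.68, even with RR 1.0. Removing the shortest cervices truncates the CL range.
- Composite of preterm birth or CL-triggered treatment: CL 0.88, CSI 0.71. CL defines part of the outcome, so this swings the other way by 0.88 - 0.71 = 0.17.

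**The case against.** The study is an exploratory feasibility study of 60 women. No hypothesis test or go/no-go rule is attached to the AUC difference. The inputs listed for the next study under Feasibility outcomes are the spontaneous preterm birth rate, the CSI variance and the recruitment rate, and a bias in the CSI-CL comparison touches none of them. Every magnitude above rests on assumed inputs, and the gap is small beside sampling error. All of this stands, and it limits how serious the point is.

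Further conditions also stand. The bias needs treatment that is triggered by CL and works at least partly; treatment given on history alone does not create it in this way. Masking of CSI is stated only for the time of the visit, and if clinicians saw and acted on it later the asymmetry would be smaller.

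A reader might also infer three stronger things that the documents do not support:

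- That readings from Visits B and C taken after treatment are pooled with untreated ones. Statistical analysis does not say which visit enters the ROC analysis.
- That no paired AUC difference is planned. The article leaves the method of comparison open, and an analysis plan that is not shown may specify it.
- That the study is likely to declare CSI superior. It plans no such test, and the 66% in Step 3 counts only which point estimate is higher.

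The objection does not remove what the article itself fixes: a comparison described as direct, without qualification, between one test that steers treatment and one that does not.

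**Conclusion.** The concern holds as a should-fix matter of analysis wording and interpretation. It is not an error that invalidates the study. If CL-triggered treatment is at least partly effective, the comparison leans towards CSI. The direction follows from the article's own account of care and masking; the size cannot be derived from it. For equally good tests, with the shortest 20% treated, RR 0.35 to 0.7 and correlation 0 to 0.8, the spurious AUC gap is about 0.01 to 0.10. It vanishes if treatment is ineffective and shrinks as the two measures become more correlated. At 60 women it is smaller than the sampling SD of about 0.12, so this study alone is unlikely to mislead through a significant result. The risk lies in a tilted estimate being carried into the larger study.

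**What to change.** In Statistical analysis, replace the unqualified direct comparison with wording such as: *CL and CSI performance will be compared descriptively under CL-guided care; because CL, and not CSI, can prompt preventive treatment, the comparison cannot support a claim that CSI outperforms CL.* Carry the same limitation into the Discussion and the results paper.

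Then:

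1. Record each CL-triggered intervention and its date from the clinical record.
2. Report the paired AUC difference with a confidence interval, alongside a sensitivity analysis that recomputes it over a range of assumed treatment effects, including none.
3. If the composite of spontaneous preterm birth before 34+0 weeks or CL-triggered intervention is shown, label it as strongly favouring CL by construction. If the untreated subset is shown, label it as still favouring CSI because it truncates the CL range.
4. Do not present restriction to pre-intervention readings as removing the bias.

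Clinical care and study visits are unchanged. The cost is a little extra data extraction and analysis, and a more qualified, less favourable statement about CSI.
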